### Data collection and handling

All source documents will be maintained by the PI. Data will be transcribed on study CRFs, and the original data will be secured by the PI and made available to the sponsor and study monitors. The PI will maintain records for 5 years. All CRF pages will be subjected to the initial inspection for omitted data, data inconsistencies, illegible data, and deviations by the study monitors. All hard copies of CRFs and media will be stored in a secure location. The PI will be responsible for submitting the following data and reports:
Adverse events (AEs): on an ongoing basis via the proper section of the CRF.Severe adverse events (SAEs) will be reported within 24 h of knowledge of the event to the sponsor and reported to IRB within 5 days, as per regulations.Any deviations, exceptions, and violations of protocol will be reported to the sponsor within 5 days and reported to IRB per their regulations.A protocol progress report will be provided to the sponsor and IRB as per regulations.A study closure report will be provided to the sponsor and IRB as per regulations.

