We formulated a novel UC-derived WJ product that has been shown to contain the essential components of regenerative medicine, namely GFs, CKs, HA, and EVs [24]. In addition, the Wharton’s jelly has been reported to contain high amounts of extracellular matrix components, including collagen, hyaluronic acid, and sulfated proteoglycans, required to improve the treatment effect [24]. That study was an essential preliminary step to better characterize the WJ formulation before performing clinical trials to determine its safety and efficacy including providing symptomatic relief to patients with grade II or III knee OA.

The goal of the proposed study is to evaluate the safety and efficacy of intra-articular injection of UC-derived WJ for the treatment of knee OA symptoms. We hypothesize that there will be no difference in the outcomes in patients receiving injection of UC-derived WJ, HA, or saline in terms of safety. We also hypothesize that patients receiving intra-articular injection of WJ will show an improvement in their overall satisfaction, Numeric Pain Rating Scale (NPRS), Knee Injury and Osteoarthritis Outcome Score (KOOS), and cartilage formation over a period of 1 year compared to the baseline visit. Our null hypothesis is that there is no difference in patients receiving either WJ, HA, or saline, and no difference between baseline and after treatment within each treatment group over a period of 1 year.

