### Assessment points

Assessments for the study period will begin at visit 1 (preliminary/baseline). The patients will be assessed using the inclusion/exclusion criteria for eligibility in the study. The participants will then undergo a physical exam (PE) on the knee diagnosed with grade II/III OA, as well as a baseline plain radiograph for an up-to-date OA grade on the KL scale and a T2-weighted MRI to obtain a Magnetic Resonance Observation of Cartilage Repair Tissue (MOCART) score. The participants will also be required to complete baseline case report forms (CRFs) including the Numeric Pain Rating Scale (NPRS), Knee Injury and Osteoarthritis Outcome Score (KOOS), and patient satisfaction/survey, SF-36. Demographic information and medical history will also be collected. The participants will then be assessed for any adverse events at visit 2.2, immediately following their respective intra-articular injection, and at their procedure visit (visit 2.1) and be re-assessed for pain using the NPRS. Through visit 3 (24 h follow-up), visit 4 (48 h follow-up), and visit 5 (1 week follow-up), patients will be reassessed for pain using the NPRS. On visit 5 (1 week follow-up), visit 6 (6 weeks follow-up), and visit 7 (3 months follow-up), participants will undergo another PE as well as have their NPRS, KOOS, and 7-point Likert scale recorded. Plain radiographs will be taken on visits 6 and 7. At this point of the study, patients in the HA or saline arms will be offered the opportunity to cross over to the WJ arm and will follow the schedule of events beginning at visit 2.2. On visit 8 (6 months follow-up) and visit 9 (1 year follow-up), patients will undergo a PE as well as have their NPRS, KOOS, 7 point Likert scale, and SF-36 taken and recorded. In addition, plain radiographs will be taken again followed by an MRI on visit 9 for a MOCART score. All participants will have the opportunity to report any adverse events at each visit or at any time within the study.

The following are the primary endpoints:
To determine the safety of umbilical cord-derived Wharton’s jelly formulation (GeneXSTEM™)To assess the patient satisfaction

The following are the secondary endpoints:
To assess the change in patient-reported outcome measures, NPRS and KOOS, from baseline and between the groups at different time pointsTo assess the cartilage formation via MOCART at 1 year time point and compare it from baseline and between the groups

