## Abbreviations

AEs: Adverse events
CKs: Cytokines
CRFs: Case report forms
EVs: Extracellular vesicles
GFs: Growth factors
HA: Hyaluronic acid
HCT/P’s: Human cells, tissues, and cellular and tissue-based products
KL: Kellgren-Lawrence
KOOS: Knee Injury and Osteoarthritis Outcome Score
SF-36: 36-Item Short Form Survey
MOCART: Magnetic Resonance Observation of Cartilage Repair Tissue
NPRS: Numeric Pain Rating Scale
OA: Osteoarthritis
SAEs: Severe adverse events
SPIRT: Standard Protocol Items-Recommendations for Intervention Trials
UC: Umbilical cord
WJ: Wharton’s jelly

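### The expedited reporting rule is worded for severe (intense) adverse events where it needs serious (consequential) ones, which leaves its scope ambiguous

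*Protocol article*

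**What the plan says.** The reporting duties are in Data collection and handling. The routine route covers every adverse event: "Adverse events (AEs): on an ongoing basis via the proper section of the CRF". The expedited route covers one category: "Severe adverse events (SAEs) will be reported within 24 h of knowledge of the event to the sponsor", and the same events are to be "reported to IRB within 5 days, as per regulations". The Abbreviations list repeats the expansion: "SAEs: Severe adverse events".

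On capture, Assessment points states: "All participants will have the opportunity to report any adverse events at each visit or at any time within the study". The first primary endpoint, in the same section, is "To determine the safety of umbilical cord-derived Wharton’s jelly formulation", and no event category is named within it. The safety hypothesis in the Background is equally general: "We hypothesize that there will be no difference in the outcomes in patients receiving injection of UC-derived WJ, HA, or saline in terms of safety".

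The term *serious adverse event* does not occur in the article. The word *serious* occurs once, in an exclusion criterion on neurological, psychological or psychiatric disorders. The article gives neither seriousness criteria nor an intensity scale for adverse events.

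**The concern.** Severity and seriousness are different axes. Severity grades the intensity of an event. Seriousness classifies its outcome or consequence, such as death, threat to life, a hospital stay or lasting disability. A rule that gets urgent information to the sponsor and the IRB should run on seriousness. This one is written on severity, and it is the only expedited rule in the article.

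What is at stake is participant protection during the trial: which events the sponsor hears of within 24 hours and the IRB within 5 days. The Discussion lists anticipated risks that could fall on either side of the distinction. Infections and immunogenic reactions may be serious without being intense at onset; injection-site pain may be intense without being serious.

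**Working it through.** The plan gives no figure on this point and no arithmetic applies. The check is a reading of every use of *severe*, *serious*, *SAE* and *adverse event* in the article.

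1. **Is it a single slip?** No. Data collection and handling and the Abbreviations list both use *severe*, and no other text corrects them.
2. **Does the article define the word so that it means *serious*?** No. No definition or seriousness criteria are given.
3. **What does the rule do if read literally?** Cross the two attributes:

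| Event | Triggers 24-hour and 5-day reports as worded | Would trigger them if worded for seriousness |
|---|---|---|
| Serious and severe | Yes | Yes |
| Serious, mild or moderate intensity | No, routine form entry only | Yes |
| Severe, not serious | Yes | No, routine form entry only |
| Neither | No | No |

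The two wordings agree in the first and last rows and disagree in the middle two. As an illustration (not an event the article describes), a hospital admission for a joint infection of moderate intensity falls in the second row; brief but intense injection-site pain falls in the third.

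4. **Are events in the second row lost to the trial?** No. The routine route has no intensity or seriousness limit, and participants can report any event at any time. Such an event is recorded and counts towards safety under either word. Only its notification changes.
5. **Does the wording enter any other calculation?** No. The sample size in Sample size and statistical analysis rests on KOOS, so power and type I error do not depend on it.

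**The case against.** The strongest reply is that *severe* was used loosely for the regulatory category. The same sentence carries the familiar acronym, a 24-hour sponsor timeline and a reference to regulations, and the article has no intensity scale that would make *severe* an operational grade. Sites also work from the full protocol and case report form, which are not shown and may hold the correct definition.

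Much of this stands. Serious events were probably meant, so the loss of expedited reporting is the result of a literal reading and not an established fact. The absence of seriousness criteria, or of an intensity field on the form, is no finding either, because an article commonly leaves these to the full protocol.

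It does not remove the point. The article states the rule and expands the acronym, both with the wrong word, so this is a misstatement and not an omission. The reference to regulations names none, and it follows the IRB clause, so it does not clearly govern what triggers the 24-hour report. If serious events were meant, the text should say so.

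Two stronger readings are tempting, and the document supports neither. A reader might infer that serious events drop out of a key category of the safety endpoint; the endpoint names no such category, and all events reach the form. A reader might also infer that counts of these events would not be comparable between sites or with other trials; the article specifies no such count as an endpoint or analysis, and one term used at up to 53 sites does not by itself show that sites would apply it differently.

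**Conclusion.** The point holds as a wording error in an operative safety rule. On a literal reading, serious events of mild or moderate intensity fall outside the 24-hour sponsor report and the 5-day IRB report, and severe but non-serious events fall inside. The consequence is limited to the scope and timeliness of notification; capture for the primary safety endpoint is unaffected.

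The number of events involved cannot be derived, because the article gives no expected event rates by intensity or seriousness. The conclusion assumes that *severe* carries its ordinary meaning of intensity and that the full protocol does not override it. If the full protocol already defines the term by outcome, what remains is an inconsistency between the article and that document. The correction is still worth making, since it concerns participant protection and costs almost nothing.

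**What to change.** In Data collection and handling and in the Abbreviations list, replace *severe* with *serious* in the expansion of SAE. Use the outcome-based meaning applied by the regulations that the rule invokes, and keep intensity as a separate attribute of each adverse event. Check that the full protocol and case report form use the same term and align them if they do not. The cost is one word in each of two places plus that check; no change to the design, sample size or analysis follows.

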### Quality control and assurance

All documents and data will be produced and maintained in such a way as to ensure control of documents and data to protect patients’ privacy as far as reasonably practicable. The sponsor, study monitor, and representatives of regulatory authorities are permitted to access the study documents (protocol, CRFs, medical records/files) as needed.

## Discussion

OA is a debilitating condition that affects millions of patients across the world, and it is estimated to drastically increase in prevalence in the upcoming years [1, 27]. OA can lead to marked pain, loss of independence, and significant health care costs [27, 28]. Currently, there are several non-operative treatment options available for grade II/III knee OA that aim to help reduce pain and enhance the quality of life, but unfortunately fail to resolve the underlying pathophysiological process of OA. These are the several reasons why the field of regenerative medicine and the use of biologics including UC-derived WJ has increased so profoundly.

The proposed clinical trial will be one of the first to examine the safety and efficacy of intra-articular administration of WJ compared to HA and saline in patients with grade II/III OA. Studies have demonstrated the efficacy of HA injections in controlling the signs and symptoms of OA, specifically in terms of pain and function, and reported safety and efficacy for the treatment of pain of OA of the knee in patients who have failed to adequately respond to conservative non-pharmacological therapy and simple analgesics such as acetaminophen [29, 30]. In addition, a recent study by Farr et al. also utilized HA as a control demonstrating the superiority of amniotic suspension allograft over HA and saline for modification of knee OA symptoms [5]. A recent meta-analysis also details the safety and efficacy of HA compared to corticosteroids for knee OA [31]. Thus, HA was chosen as a control for this proposed study.

On the other hand, despite the widespread use of HA, there is inconsistency in clinical studies pertaining to the effect of HA in knee OA. More randomized controlled trials with larger data set are required to test the efficacy of HA versus other established therapies of OA. Thus, both the Osteoarthritis Research Society International 2012 guideline and the American College of Rheumatology 2013 guidelines neither recommend nor discourage the use of HA [32]. Due to these reasons, this study is designed with an intent-to-treat, and therefore, the participants receiving HA or saline will be offered the opportunity to cross over to the Wharton’s jelly group after 3 months. Furthermore, the anecdotal evidence and unpublished case report from our team demonstrated that one injection is sufficient. The aforementioned study by Farr et al. also utilized one injection [5]. Therefore, in this study, we also proposed to utilize one injection only.

We anticipate that this study will demonstrate that intra-articular administration of WJ is safe. Some minimal adverse effects can be observed. The adverse events associated with the intra-articular administration of Wharton’s jelly will be similar to inherent risks associated with any intra-articular injection. These include pain and/or reaction at the injection site, failure of therapy to work as expected, infections, potential for contamination of the product, and unknown or unexpected reactions, including but not limited to immunogenic reactions, tumorigenic reactions, and development of autoimmune disorders. We also anticipate that patients suffering from grade II/III OA will experience improvement in their pain, function, quality of life, and overall satisfaction. In addition, we foresee that articular cartilage formation will increase over the 1-year period of the study in comparison with the baseline visit. This study has several limitations. The present investigation was designed as single-blinded rather than double-blinded. The concept of a double-blinded study was abandoned as the treating investigators can easily detect the difference in viscosity between the injectables used. Nevertheless, most of the endpoints in the study will be patient-reported, thus reducing the bias from the unblinded investigators. Another limitation of the study is the utilization of only one HA formulation: we are aware that the HA formulations with different molecular weights or cross-linking are available. Thus, the results from this study may not be applicable to other HA formulations. In conclusion, the results of this study will add to our understanding of the treatment options available for grade II/III OA and help facilitate the development of a more focused treatment strategy for patients with grade II/III OA.

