### Study design

This is a randomized, controlled, single-blind, multi-center, prospective study in which the safety and efficacy of intra-articular UC-derived WJ are compared to HA (control) and saline (placebo control) in patients suffering with knee OA. The participants in the treatment arm will receive a 2-mL intra-articular injection of UC-derived WJ (GeneXSTEM, BioIntegrate Inc., Lawrenceville, GA, USA, diluted with 1:1 sterile normal saline). The participants in the control arm and placebo arm will receive 4 mL HA (Monovisc®—4 mL injection with 22mg/mL HA, Anika Therapeutics, Bedford, MA, USA) and 4 mL of sterile normal saline, respectively. Patients in the HA group or saline group will be offered the opportunity to cross over to the Wharton’s jelly group after 3 months, as a method to aid in study recruitment and retention (Fig. 1).

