### Study interventions

After completion of visit 1 (preliminary/baseline), and determination of patient’s eligibility to be enrolled in the study, participants will be randomized into one of the three arms of the study and be scheduled for the procedure visit. At this visit, the participants will either receive an intra-articular injection of WJ (treatment), HA (control), or saline (placebo control). Following the procedure, the participants will be periodically followed for 1 year. After the 3-month follow-up visit, patients injected with HA or saline will be offered the opportunity to cross over to the WJ group. If they decide to cross over, they will receive an injection of WJ and will follow the schedule of events for the WJ injection group beginning immediately after the injection follow-up visit.

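### Control patients may take Wharton's jelly after month 3, yet between-arm comparisons run to 1 year, so contrasts after month 3 are exposed to crossover and MOCART has no crossover-free comparison

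*Protocol article*

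**What the plan says.** **The offer.** Study interventions: "After the 3-month follow-up visit, patients injected with HA or saline will be offered the opportunity to cross over to the WJ group". Those who accept are injected and then move onto the WJ visit schedule: "they will receive an injection of WJ and will follow the schedule of events for the WJ injection group". WJ patients get no corresponding offer.

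**The reason given.** Study design presents the offer "as a method to aid in study recruitment and retention". The Discussion gives another reason: "this study is designed with an intent-to-treat, and therefore, the participants receiving HA or saline will be offered the opportunity to cross over".

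**The comparisons.** The secondary endpoints in Assessment points compare NPRS and KOOS between arms over the follow-up visits, which include 6 months (visit 8) and 1 year (visit 9). They also compare MOCART between arms at 1 year. MRI is scheduled only at baseline and visit 9. The null hypothesis of no difference between the three arms, in Background, also covers 1 year.

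**The restart.** Assessment points says that crossovers "will follow the schedule of events beginning at visit 2.2", the visit straight after injection. Study interventions says that they "will follow the schedule of events for the WJ injection group beginning immediately after the injection follow-up visit".

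**Blinding.** Only patients are blinded. The Discussion's defence is that "most of the endpoints in the study will be patient-reported, thus reducing the bias from the unblinded investigators". Its list of limitations does not mention the crossover.

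**The concern.** A between-arm comparison at 6 months or 1 year is meant to show what WJ does relative to HA or saline. Once some control patients have had WJ, a comparison by randomised arm shows something else: WJ at once against a control injection with optional WJ three months later. That is a legitimate question, but it is not the one in the hypotheses. Because WJ then acts in all arms, a null result at 1 year could be pure dilution.

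Intent-to-treat does not help. It says in which arm a patient is counted; it gives no reason for offering another treatment, and it does not remove the effect of that treatment from the control arms.

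Two further problems start at the same moment. The offer goes only to patients who did not have WJ, so getting it or not getting it is informative to a blinded patient. And a crossover's visit clock starts again, so visits with the same name no longer fall at the same time since randomisation.

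**Working it through.** **Inputs from the protocol** (Sample size and statistical analysis): KOOS difference 8–10 units, also called the MCID; two-sided α = 0.05; 90% power (printed as β of 90%); at least 40 per group, raised to 56 for loss to follow-up; change from baseline to 3 months. Offer after month 3, to HA and saline only.

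**Inputs not in the protocol:** the SD of KOOS change, and the crossover uptake c. The SD is solved backwards; c is shown as a range.

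**Step 1: the plan's own figure.** Without an SD, 40 per group cannot be reproduced, only inverted. By the normal approximation:

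δ/SD = (1.960 + 1.282) × √(2/40) = 3.242 × 0.2236 = 0.725

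This gives SD = 8/0.725 = 11.0 to 10/0.725 = 13.8. The exact t calculation needs a standardised difference of 0.734; the rounded power figures at 40 per arm below are the same either way. The allowance for loss is 1 − 40/56 = 28.6%. The 3-month comparison precedes any crossover, so its 90% stands on the plan's own terms.

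**Step 2: dilution after month 3.** Suppose that a fraction c of a control arm crosses over, that each crossover has the full WJ effect by the time of assessment, and that all patients are measured on the original calendar. Then

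difference by randomised arm = (1 − c) × δ

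power ≈ Φ(3.242 × (1 − c) − 1.960), plus a negligible term from the other tail except when c is large

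n per arm to regain 90% = 40/(1 − c)²

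| Uptake c | Difference, from 8–10 | Power, 40 per arm | Power, 56 per arm | n per arm for 90% |
|---|---|---|---|---|
| 0% | 8–10 | 90% | 97% | 40 |
| 10% | 7.2–9 | 83% | 93% | 50 |
| 25% | 6–7.5 | 68% | 82% | 72 |
| 50% | 4–5 | 37% | 48% | 160 |
| 75% | 2–2.5 | 13% | 16% | 640 |

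Example at c = 50%: 3.242 × 0.5 − 1.960 = −0.339, and Φ(−0.339) = 37%. The 4–5 units left are below the protocol's own MCID. Leaving crossovers out instead keeps 20 of 40 controls at c = 50%: 0.725/√(1/40 + 1/20) − 1.960 = 0.69, power 75%. But the controls left are self-selected, so this is no longer a randomised comparison.

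**Step 3: which measures have a reading before crossover.** NPRS and KOOS are recorded up to visit 7 (3 months), so each has a clean comparison there. MOCART has one post-baseline reading, at visit 9. No analysis can give it a between-arm comparison that precedes the offer.

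**Step 4: the clock.** If the crossover injection comes about 3 months after the first, the restarted 6-month visit falls at 3 + 6 = 9 months and the restarted 1-year visit, with its MRI, at 3 + 12 = 15 months after the first injection. If the restarted schedule replaces the old one, a crossover has a scheduled reading near original month 6 (restarted visit 7, 3 + 3 = 6) but none at original month 12, which is 9 months after WJ.

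**Step 5: the blind.** Offer received means not WJ; no offer means WJ. HA and saline patients receive the same offer, so it does not separate those two arms.

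**The case against.** **The powered comparison is untouched.** Both the sample size and the interim analysis are tied to 3 months, and the endpoints affected here are secondary. This stands. A reader might infer that the trial as a whole is compromised; the protocol does not support that.

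**The size is conditional.** Uptake is not given, full WJ benefit in crossovers is assumed, and the standardised difference is carried over from a 3-month KOOS calculation to visits that were never powered. Step 4 also shows that measurement on the original calendar is not what the schedule clearly provides. All this stands. The table shows how exposure grows with uptake; it does not predict the result. With low uptake the loss is modest.

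**Intent-to-treat remains a valid analysis.** It is, for a policy of delayed optional WJ. The Discussion sentence may only be loose prose, since Study design gives the working reason. That softens the criticism of the sentence but leaves the 1-year claims where they were.

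**Handling of crossover data may be in an analysis plan not shown.** Fair, so silence on that is not held against the article. But no analysis plan can supply a MOCART reading that was never taken before crossover.

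**Stronger readings that do not hold.**
- That crossovers will be pooled with the randomised WJ arm: they join its visit schedule, but nothing puts them in its analysis set.
- That every patient learns their arm: the offer can at most show WJ or not WJ, and even this is an inference, since no section says that allocation is disclosed.
- That the two restart passages contradict each other: the Study interventions wording may be a garbled reference to visit 2.2. It is ambiguous.
- That visit-7 scores are collected after the offer: Assessment points lists them first.
- That SF-36 also loses a planned comparison: it is collected but is not a listed endpoint.

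**Conclusion.** The point holds for between-arm claims after month 3. The protocol offers the test product to both control arms at that time and still states comparisons between arms at later visits.

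- **NPRS and KOOS at 6 months and 1 year:** exposed to dilution in proportion to uptake. Under the assumptions in the table, 90% power at 40 per arm becomes 83% at 10% uptake and 37% at 50%. Scores after the offer probably come from patients who can tell WJ from not WJ, which weakens the Discussion's reliance on patient-reported endpoints.
- **MOCART:** the firmest part, because it needs no assumption about when the reading is taken. It has no between-arm comparison free of the crossover offer.
- **Visit timing:** crossovers' 6-month and 1-year visits fall at about 9 and 15 months after the first injection.
- **Justification:** intent-to-treat does not justify the crossover; recruitment and retention is the reason that Study design gives.

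A reader might conclude that every later between-arm result is invalid. The documents support less: those results are exposed, to a degree set by an uptake that is not stated, and the 3-month comparison is unaffected.

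**What to change.** Leave the crossover offer as it is, and change the claims:

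1. In Assessment points, state that month 3 (visit 7) is the last confirmatory between-arm time point. Bring the between-arm part of the null hypothesis in Background into line.
2. Label 6-month and 1-year between-arm results, including MOCART, as descriptive, with no claim about WJ versus HA or saline.
3. Report WJ data after crossover as a separate uncontrolled series, not pooled with the randomised WJ arm.
4. Remove the Discussion's derivation of the crossover from intent-to-treat, and let the reason in Study design stand.
5. Reconcile the restart wording in Study interventions and Assessment points.

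All five are changes of wording. No visit, assessment or patient is added. The real cost is giving up the 1-year between-group claims, including cartilage, which the design cannot support while the offer stands.
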